Recently, clinical studies of adults [25], neonates and infants [26], and pediatric patients with ALL [19] showed the feasibility and safety of a novel bioimpedance-based spinal needle system in LP procedures. This system, called the IQ-Tip system, measures bioimpedance at the tip of the spinal needle with 15 different frequencies and classifies the bioimpedance data 200 times in a second. This means that the tissue classification is virtually real-time (performed at every 5th ms) and the spatial sensitivity is high (~ 1 mm^3^). The system gives an audio-visual alarm when the needle tip reaches CSF in the subarachnoid space and indicates the correct location for CSF sampling or administration of intrathecal therapy. In our recent single-arm study of pediatric patients with ALL, the first attempt was successful in 80% of procedures, and the incidence of TLP was 17%. Further, neither the success rate nor the incidence of TLP was associated with the provider’s experience or the patient’s overweight [19].

Given the promising real-world clinical experience, we hypothesize that the performance of the IQ-Tip system is at least comparable to the conventional spinal needle regarding the incidence of TLP in LP procedures of pediatric hemato-oncology patients. The primary objective of the present trial is to demonstrate that the observed incidence of TLP with the IQ-Tip system will indicate either noninferiority or not only noninferiority but also superiority compared to the conventional spinal needle, which is the current standard clinical method. The secondary objectives are to compare the first puncture success rate and the incidence of complications, particularly the incidence of PDPH, in the LP procedures performed with the IQ-Tip system and conventional spinal needle. No formal hypotheses are set for the secondary outcomes.

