### Outcomes

#### Primary outcome

The primary outcome is the incidence of TLP, which is defined as ≥ 10 erythrocytes/μL of the CSF sample, conforming to the standard definition in hemato-oncology [4–14]. Hospital laboratories will routinely determine the red blood cell count (erythrocytes/ μL) from CSF with flow cytometric methods according to their standard procedures.

The incidence of TLP will be separately calculated for both study arms using Eq. 1.1$$\mathrm{Incidence\;of\;TLP}=100\times \frac{\mathrm{Total\;number\;of\;TLPs}}{\mathrm{Total\;number\;of\;all\;procedures}}\mathrm{\%}$$

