### Data analysis

Mean, standard deviation (SD), median, interquartile range (IQR), range, and proportions will be used as the main descriptive statistics as appropriate for the data. A cumulative distribution curve will be used as the main descriptive statistics for erythrocyte count data in CSF [14]. This curve illustrates the respective proportions of CSF samples, which denote the incidence of TLP for any given criterion of the erythrocyte count. For the chosen criterion, the incidence of TLP is the vertical distance (in %) from the corresponding curve point up to the 100% point.

The sample size was estimated by an online power calculator for a binary outcome in a non-inferiority trial [31]. For the estimation, it was assumed that the incidence of TLP with the IQ-Tip needle system (study arm A) is 20% and 30% with the conventional spinal needle (study arm B). The values are based on our data on the IQ-Tip system [19] and conventional needle [14] in pediatric hemato-oncology patients, respectively. Considering the 5% noninferiority margin, about 150 LP procedures in both arms will be needed to achieve 90% statistical power to demonstrate noninferiority at the significance level of *p* < 0.05. Assuming a total of 26 TLPs out of 150 procedures in the arm A, corresponding to the 17.3% incidence of TLP in our previous study [19], the total number of TLPs in the arm B should be at least 30 (20%) to demonstrate noninferiority, and at least 40 (26.7%) to demonstrate superiority for the IQ-Tip system. These relationships are illustrated in Fig. 2.

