**Fig. 2 Fig2:**
[figure not shown]
Schematic on the relation between the numbers of traumatic LP procedures (TLP) with the IQ-Tip system and conventional spinal needle required to indicate noninferiority (green area) or not (red area)

The primary statistical comparison of outcome variables will be based on the true use of the allocated spinal needles in the study LP procedures. Therefore, per-protocol analysis will be employed in the efficacy analysis as recommended for noninferiority trials [32]. The incidences of TLP and PDPH as well as the first puncture success rate between the respective study arms will be compared with the Chi-squared test. The 95% confidence intervals (95% CI) for the difference will be calculated using the exact Clopper-Pearson method. Between-arm comparisons of blood and CSF data, other performance parameters, and incidences of other complications will be performed for descriptive purposes. Definitions of the outcome variables to be used in the efficacy analysis are presented in Table 2 in terms of domain, measurement, metric, aggregation, and time point according to a recommended framework for clinical trials [33, 34]. In case of missing data, data estimation nor imputation will not be performed.

**Table 2 Tab2:** Definitions of the outcome variables (only those domains pertinent to the efficacy analysis are presented) in terms of domain, measurement, metric, aggregation, and time point

Domain	Specific measurement	Metric	Method of aggregation	Time point
Incidence of TLP	Flow cytometry	Erythrocyte count ≥ 10/µL (yes/no)	Proportion	Each study LP procedure
First puncture success rate	Provider’s self-report on CRF	Occurrence (yes/no)	Proportion	Each study LP procedure
Incidence of PDPH	Symptom diary	Occurrence (yes/no)	Proportion	Within 1 week after each study LP procedure
Peripheral blood analysis	Flow cytometry	Erythrocyte count (cells/µL) Hematocrit (%) Hemoglobin (g/L) Leukocyte count (cells/µL) Thrombocyte count (cells/µL) Existence of blasts (yes/no)	Mean Mean Mean Mean Mean Proportion	Each study LP procedure
CSF analysis	Flow cytometry	Erythrocyte count (cells/µL) Leukocyte count (cells/µL) Existence of blasts (yes/no)	Cumulative distribution curve Mean Proportion	Each study LP procedure
Number of LP attempts	Provider’s self-report on CRF	Number	Median	Each study LP procedure
Number of failed procedures	Provider’s self-report on CRF	Occurrence (yes/no)	Proportion	Each study LP procedure

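### The test and interval named for the primary outcome cannot give the intended 5-point noninferiority decision, and the plan's worked counts follow neither of them

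*Protocol article*

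**What the plan says.** All references are to the protocol article.

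- **Aim (Background, last paragraph).** The trial is to show that TLP incidence with the IQ-Tip system "will indicate either noninferiority or not only noninferiority but also superiority compared to the conventional spinal needle". No formal hypotheses are set for the secondary outcomes.
- **Outcome (Primary outcome).** "The primary outcome is the incidence of TLP, which is defined as ≥ 10 erythrocytes/μL of the CSF sample". It is binary, and lower is better.
- **Sample size (Data analysis).** The assumption is that "the incidence of TLP with the IQ-Tip needle system (study arm A) is 20% and 30% with the conventional spinal needle (study arm B"). Then: "Considering the 5% noninferiority margin, about 150 LP procedures in both arms will be needed to achieve 90% statistical power", at p < 0.05 with sidedness not given.
- **Worked counts (same paragraph, illustrated in Fig. 2).** With 26 TLPs among 150 procedures in arm A, arm B must have at least 30 for noninferiority and at least 40 for superiority.
- **Analysis (paragraph after Fig. 2).** TLP, post-dural puncture headache and first puncture success "between the respective study arms will be compared with the Chi-squared test". The next sentence is "The 95% confidence intervals (95% CI) for the difference will be calculated using the exact Clopper-Pearson method".

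No sentence in the section compares a confidence limit with the margin.

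**The concern.** The margin enters the sample size and the worked counts, but neither of the two methods that the analysis paragraph fixes for TLP.

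1. The chi-squared test asks whether the two incidences are equal. A noninferiority test asks whether arm A could be worse by 5 points or more. A non-significant chi-squared result does not answer that, and a significant one answers it only indirectly.
2. Clopper-Pearson inverts the exact test for a single binomial proportion. An analyst told to use it for a difference has to invent a way of combining two single-arm intervals, or replace the method.

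This is the trial's only confirmatory decision. If the interval and its level remain open until the data are seen, a result near the boundary (30 or 31 TLPs in B against 26 in A) can be called noninferior or not, depending on an unwritten choice.

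**Working it through.** **Inputs (Data analysis section).** n = 150 per arm; assumed incidences 20% (A) and 30% (B); margin 5 points, taken as an absolute difference because the worked counts fit that scale; A = 26/150 = 17.33%. Procedures are treated as independent throughout.

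**1. The plan's sample size.** The distance from the assumed truth to the margin is 0.10 + 0.05 = 0.15. The variance term is 0.2×0.8 + 0.3×0.7 = 0.37.

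n per arm = (z₁₋α + z₀.₉₀)² × 0.37 / 0.15²

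- One-sided 0.05: (1.645 + 1.282)² × 0.37 / 0.0225 = 141. Power at 150 is Φ(0.15/√(0.37/150) − 1.645) = Φ(3.020 − 1.645) = 91.5%.
- One-sided 0.025: (1.960 + 1.282)² × 0.37 / 0.0225 = 173. Power at 150 is Φ(3.020 − 1.960) = 85.5%.

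The stated 150 and 90% therefore reproduce at one-sided 0.05 (a 90% interval), not at the level implied by a two-sided 95% interval.

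**2. The noninferiority count (26 vs 30).** The difference is 17.33 − 20.00 = −2.67 points. SE = √(0.1733×0.8267/150 + 0.20×0.80/150) = 4.50 points.

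- 90% Wald upper limit: −2.67 + 1.645×4.50 = 4.73. Passes. At B = 29 it is 5.35 and fails.
- 95% Wald upper limit: −2.67 + 1.960×4.50 = 6.15. Fails. It is 5.54 at B = 31 and 4.93 at B = 32.
- Newcombe gives almost the same limits: 4.76 (90%) and 6.19 (95%) at B = 30, and 4.98 (95%) at B = 32.

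A count of 30 is thus a 90%-interval result. The stated 95% level needs 32.

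**3. The superiority count (26 vs 40).** The difference is −9.33 points and the unpooled SE is 4.75 points.

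- 95% Wald upper limit: −0.02. Passes.
- 95% Newcombe upper limit: +0.06. Fails; at B = 41 it is −0.56.
- 90% Wald upper limit: already below zero at B = 38 (−0.26).

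So 40 is a 95% Wald result. The two printed counts come from different confidence levels.

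**4. The stated chi-squared test at those counts (no continuity correction).**

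- 26 vs 30: pooled 56/300 = 18.67%, z = 2.67/4.50 = 0.59, p = 0.55. It says nothing about the margin.
- 26 vs 40: pooled 66/300 = 22%, SE = √(0.22×0.78×2/150) = 4.78 points, z = 9.33/4.78 = 1.95, p = 0.051. Not significant. It needs B = 41 (p = 0.038), or 42 with continuity correction (p = 0.039).

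**5. The stated Clopper-Pearson method.** It gives 11.6% to 24.4% for 26/150 and 13.9% to 27.3% for 30/150. The text gives no step from these to a difference. Subtracting opposite limits puts the upper bound at 10.4 points; a square-and-add combination puts it at 6.6. Both exceed 5, so neither reproduces the count of 30.

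| Source of the rule | Noninferiority count in B | Superiority count in B |
|---|---|---|
| Plan | 30 | 40 |
| 90% Wald or Newcombe | 30 | 38 |
| 95% Wald | 32 | 40 |
| 95% Newcombe | 32 | 41 |
| Stated chi-squared | none | 41 (42 corrected) |

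**The case against.** The strongest reply is that the intent is plain. The plan gives a 5-point margin, calls for an interval for the difference, prints counts for both conclusions, and has a figure that maps counts to noninferior or not. Ordinary Wald intervals reproduce both counts, so the sponsor evidently worked with a margin-based rule, and a separate analysis plan may word it properly. Chi-squared is also legitimate for the superiority step and for the two secondary outcomes named in the same sentence.

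Most of this stands, and it limits the point. It does not remove it. The article does not leave the method open: it names a test and an interval, and the named interval does not exist for a difference. Nor do the counts settle the rule, because they imply two different levels and one of them disagrees with the stated test.

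A reader might infer something stronger: that the plan can deliver no noninferiority conclusion at all, or that a non-significant chi-squared result would be taken as proof. Under that second reading, a needle truly worse by exactly 5 points would pass about 82% of the time (25% vs 20%) to 85% (35% vs 30%). The documents do not support it. No sentence proposes it, and the worked counts contradict it: with 26 in A, B = 15 would pass (p = 0.064), whereas the plan requires 30. Likewise, subtracting opposite Clopper-Pearson limits would need B = 40 and leave about 55% power at 20% vs 30%, but the plan does not propose that and its count of 30 rules it out. These figures describe misuse, not the plan's operating characteristics.

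**Conclusion.** The point holds as an error in the stated methods. The chi-squared test and the Clopper-Pearson interval cannot yield the margin-based decision that the plan intends, and the level is inconsistent: 95% in the analysis paragraph, but one-sided 0.05 (a 90% interval) behind the sample size and the count of 30.

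In size, this is two TLPs in arm B (30 against 32) and about 6 points of power (91.5% against 85.5% at 150 per arm). The sample size is not wrong at one-sided 0.05.

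These figures assume independent procedures and normal-approximation sample size formulas; the output of the online calculator is not shown. Repeated procedures per patient are a separate matter and could move the figures.

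**What to change.** Replace the two sentences, for TLP, with a rule such as: the primary analysis estimates the risk difference in TLP incidence (A minus B) with a two-sided interval of stated level; noninferiority is concluded if the upper limit is below +5 percentage points, and superiority is then concluded if it is below 0. Name a valid two-sample interval, for example Newcombe or Miettinen-Nurminen, or one that allows for repeated procedures per patient. Keep Clopper-Pearson for single-arm incidences, and chi-squared for secondary or descriptive comparisons only.

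Then fix one level, before the data are analysed, and bring the sample size paragraph and Fig. 2 into line:

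- **Two-sided 95%.** Restate power at 150 per arm as about 85% (or 173 per arm for 90%) and the noninferiority count as 32.
- **90% (one-sided 0.05).** Say so explicitly. The stated 90% power and the count of 30 stand. The superiority count becomes 38 if the same interval is used; if superiority is to stay at 95%, that must be said.

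Recompute both counts with the interval chosen, since they sit close to the limits. At 95%, Newcombe moves superiority from 40 to 41. The Miettinen-Nurminen score limit (constrained estimates, variance factor 300/299) is 5.01 points at B = 32, so it needs 33.

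The cost is rewording and a redrawn figure. No new data are needed unless the sponsor chooses 95% and also wants to keep 90% power. The downside of the 95% level is a slightly less favourable power statement.

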**Methods:**

The study is a multicenter, randomized, two-arm crossover noninferiority trial of pediatric hemato-oncology patients that will be conducted within the usual clinical workflow. Patients’ LP procedures will be performed alternately either with the IQ-Tip system (study arm A) or a conventional Quincke-type 22G spinal needle (study arm B). For each enrolled patient, the order of procedures is randomly assigned either as ABAB or BABA. The total number of LP procedures will be at least 300, and the number of procedures per patient between two and four. After each study LP procedure, the performance will be recorded immediately, and 1-week diary-based and 4-week record-based follow-ups on symptoms, complications, and adverse events will be conducted thereafter. The main outcomes are the incidence of traumatic LP, first puncture success rate, and incidence of post-dural puncture headache.

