### Recruitment and consent

Local study nurses or investigators will recruit participants in this trial among pediatric hemato-oncology patients of the investigational sites. All patients whose malignant disease requires multiple LP procedures in diagnostics or therapy are potentially eligible for the study. After having received written and oral information about the trial, the patient and/or parents may express their willingness to participate, sign the written informed consent, and give it to the recruiting person.

The consent applies to the use of all collected data in a pseudonymized form in scientific research, product development, and communication with authorities in potential safety and regulatory issues. Except for those mentioned in this protocol, there are no plans for ancillary studies.

The original participant’s trial information leaflet and the informed consent form, approved by the ethical committee and competent authority, are in Finnish and thus not given as supplementary material. In short, the leaflet describes the purpose and contents of the study; benefits and risks related to the study; principles of data protection, processing, and handling; voluntariness; statements of existing liability insurances and lack of incentives; and dissemination plans for the trial results.

A patient will be eligible for the trial, if:He/she is older than 1 year but no more than 18 years at the beginning of the study.His/her diagnosis or treatment plan requires multiple LP procedures for collecting CSF samples and injecting intrathecal therapy.The planned LP procedures will be performed with 22G Quincke-type spinal needlesThere are at least two LP procedures left in the patient’s treatment protocol.Both the parent(s) and the patient, depending on the patient’s age, give a signed informed consent before the first study LP procedure.

A patient will be excluded from the trial if:The parent(s) and/or the patient refuse to participate in the trial or the parent(s) and/or the patient are considered unable to give an informed consent.The provider considers the longest available spinal needle too short to perform the procedure safely.

An LP procedure of an otherwise eligible patient will be excluded from the study if:There is any temporary contraindication to LP, including but not limited to skin infection around the puncture area, unstable hemodynamics, bleeding tendency and increased intracranial pressure.

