Incidence of symptoms, complications, and adverse events	Search from hospital electronic health records	Occurrence (yes/no)	Proportion	Within four weeks after each study LP procedure

As an exploratory analysis, logistic regression analysis will be performed to assess factors that may account for the incidence of TLP, defined as a dichotomous variable (yes/no) by the criterion of ≥ 10 erythrocytes/μL. The TLP values will be obtained from the patients’ 2nd, 3rd, and 4th study LP procedures. The following dichotomous variables (yes/no) will be entered to the model as predictors: whether the preceding procedure was performed with a conventional spinal needle, whether the preceding procedure was TLP, whether the consecutive procedures were performed within a week (≤ 7 days) or two (≤ 14 days), whether the patient was obese (BMI ≥ 30 kg/m^2^), whether the provider was experienced with more than 100 previous LP procedures, and whether the thrombocyte count was less than 50,000 platelets/μL [11, 12, 14, 19]. Estimated odds ratios (OR) of the entered predictors will be reported with 95% CIs. The robustness of predictors and related ORs will be verified by performing both backward and forward regression analyses.

Statistical analyses will be done with a concurrent version of IBM SPSS Statistics for Windows (IBM Corp., Armonk, NY, USA).

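### The exploratory TLP model enters platelet count, BMI and days between LPs only as yes/no terms, although numeric values are available; precision is lost, and more so if few LPs meet a cut-off

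*Protocol article*

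**What the plan says.** The protocol article's Data analysis section introduces the model this way: "As an exploratory analysis, logistic regression analysis will be performed to assess factors that may account for the incidence of TLP". It uses only later procedures: "The TLP values will be obtained from the patients’ 2nd, 3rd, and 4th study LP procedures". The coding is fixed: "The following dichotomous variables (yes/no) will be entered to the model as predictors". Three of the listed terms are cut from quantities that can be had as numbers:

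- Interval: "whether the consecutive procedures were performed within a week (≤ 7 days) or two (≤ 14 days" (two cut-offs).
- BMI: "whether the patient was obese (BMI ≥ 30 kg/m^2".
- Platelets: "whether the thrombocyte count was less than 50,000" per µL.

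The other terms are the preceding needle, whether the preceding LP was traumatic, and provider experience above 100 LPs.

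Finer data will exist. Under Other outcomes and in Table 2, platelets are a count at each study LP. Under Descriptive data, height and weight are collected and BMI is adjusted for age. The interval follows from procedure dates. Experience is held in three categories only.

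The section promises odds ratios with 95% CIs and a robustness check by backward and forward selection. It mentions no continuous form and gives no prevalence for any cut-off.

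**The concern.** Cutting a measured quantity in two treats all values on one side as equal. If the risk of TLP changes gradually with platelet count, BMI or time since the last puncture, the yes/no term captures only part of that gradient. The loss grows as the share of LPs meeting the cut-off falls.

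An indicator with few events behind it has a very wide confidence interval and is easily removed by stepwise selection. A weak or absent term could then be taken to show that the factor does not matter, when the coding and the small group explain the result. The Background already reports that, in the earlier single-arm study, TLP was not associated with provider experience or overweight, so a further null result on BMI could be read as confirmation.

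**Working it through.** **The plan's own figure.** The protocol sets no precision target for this model. The only sample size is the noninferiority one, about 150 procedures per arm. With TLP of 20% and 30%, a margin of 5 points, 90% power and one-sided 0.05:

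n = (1.645 + 1.282)² × (0.20×0.80 + 0.30×0.70) / (0.10 + 0.05)² ≈ 141 per arm.

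At 150 per arm the power is 91.6%, so the 300 procedures are taken as given.

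**Rows in the model.** The Abstract states: "The total number of LP procedures will be at least 300, and the number of procedures per patient between two and four". Each patient's first procedure supplies no outcome, so rows = 300 − number of patients.

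| LPs per patient | Patients | Rows | TLPs at 17.3% | TLPs at 25% |
|---|---|---|---|---|
| 2 | 150 | 150 | 25.9 | 37.5 |
| 3 | 100 | 200 | 34.6 | 50.0 |
| 4 | 75 | 225 | 38.9 | 56.2 |

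The 17.3% is the earlier study's rate quoted in Data analysis; 25% is the mean of the planning rates. The list gives 6 terms, or 7 if the interval enters as two indicators. That is 25.9/7 = 3.7 to 56.2/6 = 9.4 TLPs per term.

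**Information kept by one cut.** For a normal predictor with a linear effect, a cut met by a share p keeps φ(z)²/[p(1−p)] of the information, where z is the normal quantile at 1−p.

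| Share meeting the cut-off | Information kept |
|---|---|
| 50% | 64% |
| 30% | 58% |
| 20% | 49% |
| 10% | 34% |
| 5% | 22% |
| 2% | 12% |

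**Precision if a cut-off is rarely met.** The prevalence is an assumption (3% to 10%). With 25% TLP in both groups, SE(log OR) = √(1/a + 1/b + 1/c + 1/d) from the expected 2×2 table, and the CI factor is exp(1.96 × SE).

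- 150 rows, 3%: 4.5 exposed rows, 1.1 TLPs. SE = √(1/1.125 + 1/3.375 + 1/36.375 + 1/109.125) = 1.11; factor 8.7.
- 150 rows, 5%: 7.5 exposed rows, 1.9 TLPs. SE = 0.87; factor 5.5.
- 225 rows, 10%: 22.5 exposed rows, 5.6 TLPs. SE = √(1/5.625 + 1/16.875 + 1/50.625 + 1/151.875) = 0.51; factor 2.7.

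An estimated odds ratio would thus have to lie beyond roughly 2.7 to 8.7 (or below the reciprocal) for its interval to exclude 1. These intervals are unadjusted and ignore repeated procedures in the same child; adjusted ones would generally be wider.

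**When a cut-off is commonly met.** With 200 rows, 22% TLP in the unexposed and a true odds ratio of 2, the expected CI is 1.07 to 3.74 at 50% prevalence, 1.03 to 3.88 at 30%, 0.75 to 5.32 at 10% and 0.53 to 7.6 at 5%.

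**Experience and interval.** Reducing three experience categories to two keeps about 75% to 83% of the linear-score information under the category splits tried. Entering both interval indicators keeps about 41% to 64% under the interval distributions tried.

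**The case against.** The strongest defence is that the thresholds are fixed in advance, tied to cited earlier work and clinically familiar, in a model labelled exploratory that reports confidence intervals. An imprecise odds ratio would show itself as such. The information figures also assume a linear effect: if risk rises mainly below a low platelet count, a linear term is the one that fits badly. These points stand. They make the matter minor and are a reason to keep the thresholds visible, but they do not justify leaving the measured values out of the model.

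A reader might infer three stronger claims, which the documents do not support:

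- **That the coding discards most of the information on every predictor.** Little is lost for experience. For the interval, with its two cut-offs, a loss of most of the information is not shown. For BMI and platelets it holds only if fewer than about 20%, or more than about 80%, of LPs meet the cut-off.
- **That low-platelet LPs will be rare because of the eligibility rules.** Recruitment and consent lists temporary contraindications "including but not limited to skin infection around the puncture area, unstable hemodynamics, bleeding tendency and increased intracranial pressure", but names no platelet threshold and leaves the decision to the provider. Listing the 50,000 cut-off as a predictor suggests that some such LPs are expected. Rarity is plausible for this group and for obesity, but no figure is given.
- **That the whole model is unreadable.** At 30% to 50% prevalence the intervals are wide but usable. Much of the imprecision comes from having only about 26 to 56 TLPs for 6 or 7 terms, which recoding eases but does not remove.

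**Conclusion.** The point holds as an inexpensive improvement to an exploratory analysis. The protocol fixes yes/no coding for three predictors that can be used as numbers. Under a roughly normal predictor and a linear effect, a single cut costs at least about 36% of the information (100% − 64%), and 66% to 78% if only 10% to 5% of LPs meet it. If BMI ≥30 or platelets below 50,000/µL occurs in 3% to 10% of LPs, that odds ratio rests on about 1 to 6 TLPs, with a CI factor of 2.7 to 8.7 either way. A real gradient could then be missed or dropped by selection. The prevalence range is an assumption, and the shape of the true effects is unknown. Nothing here touches the primary noninferiority comparison.

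**What to change.** In the main exploratory model, enter platelet count (log scale), age-adjusted BMI and days since the previous LP (log scale) as continuous terms. Show TLP rates by the cited cut-offs (below 50,000/µL; obese; ≤7 and ≤14 days) descriptively, or fit them as a secondary model, so that threshold effects and comparability with earlier work remain visible. Using the three collected experience categories is optional.

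The cost is a wording change; the data are already to be collected. Odds ratios would be per unit or per doubling, which is less familiar than yes/no, and would assume an approximately linear effect on the chosen scale. The report should also say that the small number of TLPs limits precision whichever coding is used, and that a non-significant or dropped term is not evidence that the factor has no effect.

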## Materials and methods

### Trial design and setting

The present study (acronym IQ-LP-04) is a multicenter, randomized, two-arm crossover noninferiority trial of pediatric hemato-oncology patients. Since the patients act as their controls in the cross-over design, the potential bias due to variability between the patient characteristics is effectively controlled for. The two study arms refer to performing the patient’s LP procedures alternately using the IQ-Tip system (study arm A) or a conventional spinal needle (study arm B). The arm of the first study procedure will be randomly assigned, while the number of procedures per patient will be between two and four. Thus, the two possible randomly assigned sequences of the study LP procedures are ABAB and BABA.

All study LP procedures are part of patients’ preplanned LP procedures without additional procedures or laboratory tests. Only the data needed for the management of patients’ malignant diseases will be collected as part of routine therapy and evaluation, independent of the present trial. Biological specimens for genetic or molecular analyses will not be collected. If the patient’s treatment or medical condition requires concomitant care, modification, or other interventions during the study, they will be permitted. The crucial point for the study is that the allocated spinal needles are used in the study LP procedures as intended. Patients’ treatments and care will continue as planned after completing the trial or withdrawing from the study due to any reason. There are no specific plans for promoting participant retention during the study. The pragmatic nature of the present trial is expected to promote complete follow-up and acquisition of data.

After each study LP procedure, there will be a 1-week follow-up using a symptom diary and a 4-week follow-up of hospital electronic health records. The flow chart of the study LP procedures is shown in Fig. 1, whereas the schedule of enrolment, study LP procedures, and assessments during the post-allocation period are outlined in Table 1. This protocol has been written according to the SPIRIT reporting guidelines [27] and verified against the SPIRIT checklist.

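### The exploratory TLP regression has no patient effect, so its odds ratio for a preceding traumatic LP can exceed 1 from patient differences alone and should not be read as an effect of the earlier LP

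*Protocol article*

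**What the plan says.** In the Data analysis section of the protocol article, an exploratory "logistic regression analysis will be performed to assess factors that may account for the incidence of TLP". The rows are fixed: "The TLP values will be obtained from the patients’ 2nd, 3rd, and 4th study LP procedures". So is the predictor list. It includes the needle type used at the preceding LP, "whether the preceding procedure was TLP, whether the consecutive procedures were performed within a week (≤ 7 days) or two (≤ 14 days", provider experience, and two patient-related terms, "whether the patient was obese" and "whether the thrombocyte count was less than 50,000" per μL. On reporting: "Estimated odds ratios (OR) of the entered predictors will be reported with 95% CIs". The only robustness check named is backward and forward selection. No patient effect is listed.

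Under Trial design and setting, the crossover is justified by patients serving as their own controls, so that "the potential bias due to variability between the patient characteristics is effectively controlled for".

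**The concern.** The preceding-TLP predictor is an earlier value of the outcome in the same patient. A patient who tends to have traumatic LPs for any lasting reason will tend to score yes both as predictor and as outcome. Without a patient effect, the model attributes that tendency to the preceding LP.

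An odds ratio of 1 for this term therefore needs two conditions together: the earlier LP has no effect, and patients do not differ in TLP risk beyond the listed covariates. The second sits uneasily with the plan's own reason for using a crossover.

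The stated aim is to find factors that may account for TLP. A reader of the results could conclude that a traumatic LP raises the risk of the next one when no such effect exists.

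**Working it through.** **The plan's own figures.** The protocol gives no figure for this model. The inputs come from its sample-size paragraph: TLP 20% (arm A) and 30% (arm B), a 5% margin, and about 150 LPs per arm for 90% power. These agree with each other at one-sided 5%: power = Φ(0.15/√((0.21 + 0.16)/150) − 1.645) = 91.6%.

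**Rows.** With 300 LPs and two to four per patient, the model has 75 × 3 = 225 rows (four LPs each), 100 × 2 = 200 rows (three each) or 150 × 1 = 150 rows (two each).

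**Assumption.** The within-patient correlation is not in the documents. It is expressed as a latent intraclass correlation (ICC) and varied from 0 to 0.4.

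**Population odds ratio with no effect of the earlier LP.** Let logit P(TLP) = β(needle) + u, with u ~ N(0, σ²) per patient and σ² = ICC/(1 − ICC) × π²/3. Set β to give 20% in A and 30% in B. Because needles alternate, consecutive LPs are always one A and one B. With p₁₁ = E[p_A(u) p_B(u)],

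OR = p₁₁(1 − 0.20 − 0.30 + p₁₁) / [(0.20 − p₁₁)(0.30 − p₁₁)].

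The same OR applies to A after B and to B after A, and the previous-needle term identifies the current needle, so the arm difference does not create the bias. At ICC 0.2, σ = √(0.25 × 3.29) = 0.907 and p₁₁ = 0.275 × 0.30 = 0.0825, so OR = 0.0825 × 0.5825/(0.1175 × 0.2175) = 1.88.

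| Latent ICC | σ | TLP in A after a TLP | TLP in A after no TLP | OR |
|---|---|---|---|---|
| 0 | 0 | 20.0% | 20.0% | 1.00 |
| 0.1 | 0.605 | 23.7% | 18.4% | 1.38 |
| 0.2 | 0.907 | 27.5% | 16.8% | 1.88 |
| 0.3 | 1.187 | 31.4% | 15.1% | 2.57 |
| 0.4 | 1.481 | 35.3% | 13.4% | 3.52 |

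**Trial-sized samples.** In 2,000 simulated trials per setting, an ordinary logistic model was fitted with the plan's predictors (one interval term; covariates other than needle and preceding TLP unrelated to outcome). The table gives the chance of a significant OR above 1, nominally 2.5%, with no true effect.

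| Layout | ICC 0 | ICC 0.1 | ICC 0.2 | ICC 0.3 |
|---|---|---|---|---|
| 75 patients × 4 | 3.1% | 15.1% | 42.9% | 71.6% |
| 100 × 3 | 2.4% | 14.3% | 40.5% | 68.0% |
| 150 × 2 | 2.8% | 11.9% | 33.5% | 60.4% |
| 75 × 4, cluster-robust errors | 3.2% | 14.4% | 39.0% | 66.1% |

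Cluster-robust errors barely help because the estimate itself is displaced, not only its standard error. Backward and forward selection cannot detect this; a displaced predictor is simply retained more often.

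**Which remedy works.** Random-intercept models were fitted to 10,000 simulated patients with four LPs and no true effect:

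| Model | OR at ICC 0.1 | 0.2 | 0.3 |
|---|---|---|---|
| Random intercept, LPs 2 to 4 only | 1.33 | 1.46 | 2.10 |
| Same, plus first-LP TLP status | 1.04 | 1.09 | 0.95 |
| All LPs, including the first, modelled jointly | 1.08 | 1.07 | 1.03 |

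A random intercept alone is not enough, because the first outcome depends on the same patient intercept.

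**Precision of the remedy.** For the model with first-LP status at ICC 0.2 and 25% TLP (300 runs), power against a true OR of 2 is 24% (75 × 4) or 12% (100 × 3), and against an OR of 3 it is 48% or 25%. With no effect, the central 95% of estimated ORs runs from 0.31 to 2.97 (75 × 4) and from 0.15 to 3.48 (100 × 3).

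**The case against.** The strongest reply is that the model is labelled exploratory, calls its variables predictors and attaches no decision to any odds ratio. As a prognostic statement the odds ratio is right: a child with a previous TLP is at higher risk of another, whatever the reason. This stands, and it limits the point to interpretation. It does not dispose of it, because the stated aim is explanatory.

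A second reply is that a condensed article may leave the handling of repeated rows to the full protocol or analysis plan. Silence on clustering alone would indeed be no finding. Here, however, the rows, the predictor list and the robustness check are all stated, and it is their combination that misleads. Adjusting only the standard errors elsewhere would not correct it.

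A third reply is that the evidence for patient heterogeneity is thin. This is partly right. The Background's list of high BMI, anatomic abnormality, young age and many failed attempts concerns referral for ultrasound, not bleeding risk. Obesity and platelets are in the model and may absorb some of the difference. The earlier single-arm study found no association of TLP with overweight; that weakens weight as a source of heterogeneity, but also suggests the obesity term will absorb little. The crossover rationale is general and gives no figure.

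Stronger readings are tempting but unsupported. A reader might infer that the primary comparison is biased; it does not use this model. A reader might take the regression as the trial's formal carry-over test and fault it for not isolating residual blood after a short gap; the section names neither carry-over nor residual blood. A reader might expect a false signal as a matter of course; that depends on an ICC the documents do not give.

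**Conclusion.** The point holds as one of interpretation and model specification in an exploratory analysis. With no effect of the earlier LP, the planned odds ratio for a preceding TLP would be about 1.4, 1.9 and 2.6 at a latent ICC of 0.1, 0.2 and 0.3, and 1.0 at ICC 0. With 75 patients and four LPs each, it would be significantly above 1 in about 15%, 43% and 72% of trials at those three positive values.

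These figures rest on the plan's 20% and 30% rates, a normally distributed patient intercept, and heterogeneity not captured by the listed covariates. Any part that obesity or platelets absorb would reduce them. The primary noninferiority conclusion does not depend on this model. The change is worth making because the planned output cannot support an explanatory reading and most of the remedy is wording.

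**What to change.** In the exploratory regression paragraph of Data analysis:

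1. State that the odds ratio for a preceding TLP from the ordinary logistic model marks a TLP-prone patient and will not be read as an effect of the previous LP.
2. Add, as a sensitivity analysis, a mixed-effects logistic model with a patient random intercept that also handles the first LP, either with first-LP TLP status as a covariate or by modelling all LPs jointly.
3. Base any statement that one LP affects the next only on that sensitivity model.

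A product term between preceding TLP and a short interval is optional; it answers a question the plan does not pose.

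The cost is a few sentences and one further model on data already collected. The real drawback is precision. In every 2nd-LP row, first-LP status and preceding-TLP status are the same variable, so patients with only two study LPs add almost nothing to separating them, and the confidence interval will be wide. The report should say so, and should not present a non-significant result as evidence that one LP does not affect the next.
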